#### Perceptions of School Safety

The “Safe and Responsive Schools” Safe School Survey [65] is a validated tool designed to be administered to students and school staff. This instrument assesses six critical constructs, including perceptions of school climate, school safety, and belongingness. In line with previous research on school violence and in an effort to comprehensively assess perceptions of school safety, this tool seeks to capture both minor conflicts (eg, arguments among students) as well as more significant forms of disruption (eg, weapon possession on school grounds). Each student survey will include items from the Safe School Survey, which has a 5-point Likert scale response option [65]. Each teacher survey will include items from the Safe School Survey designed for school staff, which has a 5-point Likert scale response option [65]. Furthermore, each principal survey will also include items from the Safe School Survey designed for school staff [65].

#### Educational Outcomes

Among the participating students in each school, self-report survey data on academic engagement will be assessed via 4 items stemming from the Student Engagement Instrument [66,67]. The Student Engagement Instrument is a survey that assesses extrinsic motivation to learn, future goals and aspirations, class participation, teacher-student relationships, and perceived peer support for learning [66,67]. We will also include 1 multiple-choice item that has been adapted from the Centers for Disease Control and Prevention’s Youth Risk Behavioral Surveillance System that asks students to describe their academic grades in schools over the past 12 months [68].

#### School Safety and Security

Data on school safety and security strategies for each participating school will be collected via 2 sources. First, principals from all participating schools will be surveyed on their knowledge of current school safety tactics and policies. Data on school safety and security indicators under the following seven categories will be assessed: (1) external target hardening efforts (eg, monitored school entry doors and signs indicating the school is a “Gun Free School Zone”); (2) internal target hardening efforts (eg, metal detectors and security cameras); (3) student or staff monitoring (eg, threat assessment team and zero-tolerance policies for weapons); (4) emergency procedures or drills (eg, written active shooter plan); (5) emergency notification technologies (eg, anonymous thread reporting systems and panic buttons); (6) medical support (eg, full or part-time school nurse on campus); and (7) school security staff (eg, law enforcement officers or police and teachers and other personnel armed with guns). Each multiple-choice item will include the following response options: “Yes, this policy/practice is active now at my school,” “No, this policy/practice is not active at my school,” or “Don’t know/No answer.” It should be noted that several of these survey items were adapted from the School Survey on Crime and Safety that is administered via the National Center for Education Statistics to a nationally representative sample of schools to assess whether individual schools are or are not implementing a range of school safety and security interventions [69]. First, for each school, a summative score will be generated that accounts for the number of policies or practices that each principal responded with “yes.” Second, and especially if the principals do not necessarily have the time and capacity to review the safety details via a survey, we will review each school’s current school safety plan, which is a comprehensive document developed by the school stakeholders that details preparation and response protocols to various school emergencies (ranging from bullying prevention efforts to fire safety drills and active shooter scenarios). A thorough review of each school’s safety plan will allow our team to validate the data collected about current school safety strategies and also fill in any missing data. Should there be any discrepancy between the data provided by the principal and the protocols detailed in the school safety plan, the study team will defer to the data provided via the school safety plan.

#### Active Shooter Drills

Given the ubiquity specifically of active shooter drill implementation across secondary schools in the United States [15], we will identify each school’s active safety drill protocol via the school’s safety plan in our school recruitment effort for both exposure and nonexposure schools, and subsequently in our analyses. Specifically, we will identify whether our schools are currently implementing the Standard Response Protocol [70], which is the most widely implemented active shooter drill protocol in schools across the United States and involves high student-teacher preparedness and processing, versus other types of drill protocols [71] that may involve low student-teacher preparedness, a surprise element to the protocol, and more realistic portrayals of violence built into the drill. This will help us to identify and subsequently classify schools in our sample with two varying types of active shooter drill implementation.

#### Independent Covariates

Multiple independent covariates will also be collected via data sources like the National Center for Education Statistics and the US Census and adjusted for in conditional logistic regression models [72,73]. These covariates will include the length of time since the school experienced a shooting, demographics (eg, urbanicity, school level, and type of school), and school district characteristics. In addition, secondary data on education access, equity, and school discipline will be directly downloaded from the Civil Rights Data Collection website [74]. Using these recent data on each participating school, the study team will create a “school discipline” summative score that will comprise the following indicators (accounting for school population size and reflecting the number per academic year): attendance rate, number of in-school suspensions, out-of-school suspensions, students referred to law enforcement, students disciplined for harassment or bullying, and school-related arrests. Propensity score match and control statistical methods will be used to ensure rigor in association validity, controlling for these characteristics comprehensively.

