#### Exposure School Selection

Our research team is identifying all possible intentional school shooting cases via a comprehensive review of multiple national school shooting databases, including the K-12 School Shooting database, the Everytown for Gun Safety database on gunfire on school grounds, and the Washington Post database on school shootings, to identify all schools that have experienced intentional gunfire on campus during school hours [51]. These data document all incidents in which a gun is fired or a bullet hits school property for any reason, regardless of the number of victims, time, or day of the week. Our research team is then coding this list of incidents to identify cases that meet the criteria for intentional school shooting at a secondary (ie, middle or high school level) public school—all cases of intentional gunfire on school property, occurring during school hours (including 1 hour before official school activities begin and 1 hour after all official school activities end), beginning January 1, 2015—to ensure we have enough schools in our sampling frame that meet our aforementioned criteria. We are excluding accidental discharges and attempted suicides where no other person was targeted or shot. We are also excluding any incidents taking place on a school bus and on school property that are noncontiguous with the school’s primary campus. Furthermore, we are cross-referencing our list of incidents with other publicly available data sources [40] to ensure that no incidents meeting our criteria are missed. Two members of our research team are then independently coding this list of incidents to identify the cases that meet our proposed study’s criteria for “intentional school shooting”; a third member of our study team is reviewing any potential discrepancies in coding efforts. The final list of exposure schools will then be divided into 2 based on recentness, that is, schools where the incident happened between January 1, 2015, and December 31, 2021, and schools where the incident happened between January 1, 2022, to December 31, 2023. In total, 3 schools will be randomly selected from each list. In case a school declines to participate, we will move to the next randomly selected school. Nonexposure schools will be matched to the final exposure schools. In case a school declines to participate, we will move to the next randomly selected school.

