### Data Organization and Treatment

#### Survey Data Entry

All survey data collected in this study are being recorded initially in Excel (Microsoft Corp) for organization and management and then subsequently read into SPSS (version 29.0; IBM Corp) for analysis [76]. The study team maintains a codebook; variables will be recoded where needed and summative scores will be computed.

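### The discipline covariate is not tied to a pre-incident year, and the safety-plan rule does not stop unmentioned measures being scored as absent

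*Protocol article*

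**What the plan says.** **Discipline score (Independent Covariates).** The article says "the study team will create a “school discipline” summative score that will comprise the following indicators": "attendance rate, number of in-school suspensions, out-of-school suspensions, students referred to law enforcement, students disciplined for harassment or bullying, and school-related arrests". The stated scaling is "accounting for school population size and reflecting the number per academic year". On timing it says only "Using these recent data on each participating school". The section then commits to propensity score and control methods covering these characteristics in full. Under Survey Data Entry it adds: "The study team maintains a codebook; variables will be recoded where needed and summative scores will be computed".

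**Incident dates (Exposure School Selection).** The exposure schools are split into "schools where the incident happened between January 1, 2015, and December 31, 2021, and schools where the incident happened between January 1, 2022, to December" (the second window closes at the end of 2023), with three schools drawn from each list. Results gives January 2024 as the start of data collection.

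**Safety score (School Safety and Security).** The score counts the practices that the principal reports as currently in force. The safety plan is then used to check those answers and fill gaps. If the two sources differ, "the study team will defer to the data provided via the school safety plan". The plan is called comprehensive and is described as a document that "details preparation and response protocols to various school emergencies". Under Document Review, two team members independently determine from the plan whether each strategy is being implemented. No separate code for a strategy that the plan does not mention is described.

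**The concern.** **Timing.** Question 1 compares schools with and without a shooting. Suspensions, referrals, arrests and attendance may all change after a shooting. If they are measured afterwards and then used for adjustment or matching, part of the effect under study can be removed, and the contrast no longer has a clear interpretation. If the data year falls after the incident in one exposure list and before it in the other, the recent versus less recent comparison is adjusted for different things in its two arms.

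**Safety score.** This is the main independent variable of questions 2 and 3. There is one score per school, so it takes at most 12 values. The items include cameras, metal detectors, a nurse and armed staff, which an emergency-procedures document need not list. Plans that inventory equipment would keep their points and plans confined to procedures could lose them. The error would then differ between schools, and a few wrong values out of 12 can move a slope.

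**Attendance.** One indicator that is good when high sits in a single sum with five that are bad when high.

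**Working it through.** The article gives no numerical value for either score, so there is no stated figure to reproduce. The check is of the order of events, plus illustrations on assumed inputs.

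**1. Order of discipline data and incident.** Inputs from the article: incident windows 2015-2021 and 2022-2023, and data collection from January 2024. The discipline data year is not given, so I vary it, assuming a school year that runs from late summer to early summer.

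| Assumed data year | 2015-2021 incidents | 2022-2023 incidents |
|---|---|---|
| 2020-21 | Data follow the incident for 2015 to mid-2020; mixed or earlier after that | Data precede every incident |
| 2021-22 | Data follow the incident to mid-2021; mixed for autumn 2021 | Mixed for early 2022; data precede the rest |
| 2022-23 | Data follow every incident | Data follow incidents before autumn 2022, are mixed to mid-2023, and precede the rest |

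Under each assumption, most of the 2015-2021 window lies before the data year, so the score is post-incident for most dates in that list. For the 2022-2023 list the answer changes with the assumed year. Three of the six exposure schools come from each list, so a single recent year can give a post-exposure covariate in one half and a pre-exposure covariate in the other.

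**2. Safety score if silence is coded as absence.** Assume 15 measures are truly active and the plan mentions a share *m* of them. Score = 15 × *m*.

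- *m* = 1.0: 15
- *m* = 0.8: 12
- *m* = 0.6: 9
- *m* = 0.4: 6

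Two schools with identical practice could differ by up to 15 − 6 = 9 points over this range because of how their plans are written. Both the 15 and the shares are assumptions.

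**3. Attendance in the sum.** On a raw percentage plus per-100 scale, with assumed values in the order the indicators are listed:

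- Low-burden school: 95 + 2 + 2 + 0.2 + 0.5 + 0.1 = 99.8
- High-burden school: 88 + 5 + 5 + 0.6 + 1 + 0.3 = 99.9

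With attendance replaced by absence (5 and 12), the sums are 5 + 4.8 = 9.8 and 12 + 11.9 = 23.9.

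With standardised indicators that share one factor with loading λ, the correlation of the sum with the underlying burden is:

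- attendance not reversed: 4λ / √(16λ² + 6(1 − λ²))
- attendance reversed: 6λ / √(36λ² + 6(1 − λ²))

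| λ | Not reversed | Reversed |
|---|---|---|
| 0.5 | 2.0/√8.5 = 0.69 | 3.0/√13.5 = 0.82 |
| 0.7 | 2.8/√10.9 = 0.85 | 4.2/√20.7 = 0.92 |
| 0.9 | 3.6/√14.1 = 0.96 | 5.4/√30.3 = 0.98 |

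A simulation with the same assumptions agrees. An unreversed attendance term loses almost all separation in the raw-sum example, but only weakens a standardised score and does not invert it.

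**The case against.** Three stronger readings are tempting, and the article supports none of them.

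- **That the discipline data come from after the shooting.** The article says only that they are recent. With incidents up to the end of 2023, the data for the later list may well precede the event. It is also an inference that the score enters question 1: the analyses of covariance adjust for key covariates that are not named, and the covariates section links its variables to conditional logistic regression and propensity methods. What stands is that no year is tied to the incident and that the commitment to control for these characteristics is broad, so nothing keeps a post-incident score out of the shooting contrast.
- **That a silent plan overrides a principal's yes.** Silence is never mentioned. The discrepancy rule compares the principal's data with the protocols that the plan sets out, and a plan that says nothing about cameras sets out no protocol on them. On that reading there is no discrepancy and no problem. The plan is also double-coded. What stands is that Document Review describes a determination of implemented or not, without a third category, so the harmful reading is not excluded.
- **That schools are actually mis-scored because attendance is added as it stands.** The article does not say that raw values are summed, and it provides for recoding where needed. Reverse-coding is ordinary codebook detail. Most of this objection stands.

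A fair point against moving all discipline data to a pre-incident year is that, for questions 2 and 3, current discipline is the relevant confounder of current practices and current mental health. For a 2015 incident, a pre-incident value is also at least nine years older than a 2024 survey. The fix below allows for this.

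**Conclusion.** The concern holds in limited form.

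1. **Timing** is a real weakness in a method the article does fix. Controlling for a recent discipline score probably means conditioning on post-incident data for many of the 2015-2021 schools. For the 2022-2023 schools this depends on the unstated data year. The resulting bias in question 1 cannot be sized from the article. It rests on discipline or attendance responding to the shooting and on the score entering the question 1 adjustment or the propensity score.
2. **The safety-plan rule** is open to a reading that lowers the main independent variable of questions 2 and 3. The illustrative loss is 3 to 9 points out of 15, if 40% to 80% of active measures are mentioned and silence is coded as absence. The article neither states nor rules out that coding.
3. **Attendance** is a request for clarification only. Actual mis-scoring is not shown.

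The first two should be settled before the scores are computed. Three of the 12 schools had been surveyed by May 2024.

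**What to change.** 1. **Discipline score.** For the shooting versus no-shooting contrast (question 1 and any propensity score), use the last available school year before the incident, and the same year for the matched nonexposure school; or leave the score out of that contrast. Keep current discipline data for questions 2 and 3. Cost: older data may be less complete and further from the survey date, and two versions of the score must be kept.
2. **Safety score.** Let the plan override the principal only where it explicitly contradicts the answer. Code a measure that is not mentioned separately and keep the principal's answer. Add a sensitivity analysis using principal answers alone. Cost: one extra code on the plan extraction form, recoding of any plans already reviewed, and one additional analysis.
3. **Attendance (minor).** State that attendance enters as an absence rate and that the six indicators are put on a common scale before they are combined. Cost: one sentence in the codebook or analysis plan.

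None of these changes needs new data from participants.

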### Data Collection Procedures

#### Students

Participating students in each school will complete 1 web-based survey administered on the web via Qualtrics (Qualtrics, LLC) [75], which is an web-based survey platform. This survey will take approximately 10 to 12 minutes to complete.

#### Teachers

Participating teachers will complete 1 on the web, also via Qualtrics, that will take approximately 10 to 12 minutes to complete.

#### Principals

Participating principals will complete one 10- to 12-minute survey, again via Qualtrics. As part of the principal survey, we will be asking them to provide a copy of their school’s current school safety plan.

### Ethical Considerations

#### Protection for Human Subjects

This study protocol (protocol #21-149) underwent a full board review and has been approved by the institutional review board (IRB) at Teachers College, Columbia University. Details on data confidentiality and privacy protections, informed consent descriptions, the study’s inclusion criteria, and participant compensation are noted in the following sections.

#### Data Privacy and Confidentiality Protection

Survey data collected from students, teachers, and school staff will be confidential. All participants will be associated with a specific school. However, no identifying names or any other identifiers will be used at any point in the study. Each participant will be identified solely via an alphanumeric code during the data collection and organization process. This will be used solely for matching the survey data to the appropriate school for analyses. No information about any individual student or staff will ever be reported or shared. Furthermore, all survey data will be reported in aggregate.

#### Informed Consent Descriptions

As described in the participant recruitment section, all potential participants will engage in a thoughtful informed consent process. Parents and guardians of all students will have the opportunity to provide consent, if they choose, for their child to participate in this study. Similarly, the potential teacher and principal participants will also complete a consent form before participation. These consent forms, all also approved by the Teachers College, Columbia University IRB, review in clear language the purpose of the proposed study, what each participant will be asked to do if they agree to participate, any potential risks, discomforts, and benefits each participant might expect from taking part in the study, details about the study’s confidentiality, how the results will be used, and the co-PIs’ contact information should any questions arise during this process. For those students whose parents provide consent for them to participate, they then will have the opportunity to complete an assent form before participating in the study’s survey. The assent form for the students similarly and clearly describes the purpose of the research, what the student can expect during the study itself, any consequences associated with participating in this study, how we will take care to protect their data privacy and confidentiality, the co-PIs’ contact information should any questions arise, and also a statement underscoring that participation is completely voluntary and that the student does not have to participate.

#### Inclusion

The literature that has been synthesized for this study elucidates the critical role that members of minority groups, members of both sexes, and children all play in a study like this. Thus, members from all 3 groups are included.

#### Compensation

Each participating school will receive a US $250 gift card to Amazon for the school to put toward books or other school supplies. Following participation in the study, the study’s co-PIs will send the electronic gift card directly to the participating school’s principal.

### Data Organization and Treatment

#### Survey Data Entry

All survey data collected in this study are being recorded initially in Excel (Microsoft Corp) for organization and management and then subsequently read into SPSS (version 29.0; IBM Corp) for analysis [76]. The study team maintains a codebook; variables will be recoded where needed and summative scores will be computed.

#### Document Review

Each school safety plan will be reviewed and coded independently by 2 members of our research team to determine if each of the school safety strategies and tactics of interest are being implemented. These data will also be recorded initially in Microsoft Excel for organization and management and then subsequently read into SPSS for analysis.

#### Missing Data

Consistent with previous research, we estimate the majority of survey items to have <10% missing data and no more than 19% missing survey data on any given item [58]. However, should higher levels of missing data occur, multiple imputation methods will be used [77].

### Data Analysis Plan

The data collected from the students, teachers, and principals across all 12 participating schools will be analyzed and will fully respond to each of the research questions. Descriptive statistics will be calculated to summarize student and teacher participant characteristics within each school and also describe each school’s safety and security strategies. Analyses of covariance will subsequently be used to identify potential significant differences in the prevalence of mental health and well-being, perceptions of school safety, educational outcomes, and ACEs among students in schools that have more recently experienced an intentional school shooting, schools that have experienced an intentional school shooting less recently, and schools that have never experienced a shooting, while controlling for key covariates.

ANOVA will also be used to identify potential significant differences in the prevalence of mental health and perceptions of school safety among teachers in schools that have more recently experienced an intentional school shooting, schools that have experienced an intentional school shooting less recently, and schools that have never experienced an intentional school shooting. We used G^*^Power (version 3.1; Heinrich Heine University Düsseldorf) to run power analyses in anticipation of our proposed analyses, assuming an α level of .05 and a power of 0.80. In the case of our proposed student analyses, a very small minimum effect size will need to be detected to meet our power requirements and given our anticipated minimum sample size (exposure schools: N=500-600, nonexposure schools: N=500-600). In the case of our teacher analyses, a medium effect size will need to be detected and given our anticipated minimum sample size (exposure schools: N=30-60, nonexposure schools: N=30-60). On the basis of the average enrollment across secondary public schools in the United States, we should be able to reach the minimum sample size from 12 schools.

Multiple regression analyses will then be used to determine if the strength of the association between school safety interventions and mental health outcomes differs among students and school staff in schools with varying levels of trauma exposure. Mediated moderation analyses will evaluate the role of ACEs on the relationships between exposure to an intentional school shooting, exposure to school safety strategies, and student outcomes (ie, mental health and well-being, perceptions of school safety, and educational outcomes) [78]. Again, power analyses revealed that for our student-level analyses and given an α level of .05 and a power of 0.80, a small effect size will need to be detected to meet our power and sample size requirements. In the case of our proposed teacher analyses, a medium effect size will need to be detected. It should be noted that these values reflect conservative estimates with regard to student and staff recruitment. Thus, we are confident that we will achieve reasonable power to fully answer all of our questions and achieve the specific aims of the study.

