## Methods

### Sampling Frame

#### Study Design

This is an observational study that will involve collecting cross-sectional survey data from a national sample of students, teachers, and principals from 12 secondary public schools across the United States. Our sample includes participants from 6 randomly selected exposure schools: secondary schools that have recently experienced an intentional school shooting (<2 years ago) and secondary schools that have experienced an intentional school shooting less recently (>2 years ago). Of the schools in our dataset that meet these criteria, we are randomly selecting schools to participate in our study from the group of eligible schools. If a school does not express interest in participating, we are replacing that school with another eligible school in our dataset. We are then matching our exposure schools to 6 randomly selected nonexposure schools: 6 secondary public schools that have never experienced a school shooting. We are matching the nonexposure schools to exposure schools on the following key variables: state, urban or nonurban status, and school level (ie, middle or high school).

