#### Demographics

Data on sex, race, age, grade-level, and presence or not at the time of the school shooting incident for students in the exposure school will be provided by each student at the beginning of the survey. Self-report data on teacher and principal demographics (eg, their length of time working at the school) will also be collected at the beginning of the teacher and principal surveys, respectively.

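### The teacher comparison across the three exposure groups is specified as an unadjusted ANOVA, which leaves it open to residual confounding that a short list of teacher covariates could reduce cheaply

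*Protocol article*

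**What the plan says.** All references are to the Protocol article.

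- **Data Analysis Plan, students.** "Analyses of covariance will subsequently be used to identify potential significant differences in the prevalence of mental health and well-being", perceived safety, educational outcomes and ACEs across three groups of schools (recent shooting, less recent shooting, never), "while controlling for key covariates".
- **Data Analysis Plan, teachers.** "ANOVA will also be used to identify potential significant differences in the prevalence of mental health and perceptions of school safety among teachers" across the same three groups. No covariates are mentioned and no reason is given for the different method.
- **Study Design.** "This is an observational study that will involve collecting cross-sectional survey data from a national sample of students, teachers, and principals". Some control comes from the design: "We are matching the nonexposure schools to exposure schools on the following key variables: state, urban or nonurban status, and school level".
- **Independent Covariates.** School and district covariates are to be "adjusted for in conditional logistic regression models". The section ends more broadly: "Propensity score match and control statistical methods will be used to ensure rigor in association validity, controlling for these characteristics comprehensively".
- **Demographics.** "Self-report data on teacher and principal demographics (eg, their length of time working at the school") are collected in the surveys.

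**The concern.** The same non-randomised contrast gets two methods in consecutive paragraphs, and only the student one is adjusted. An analyst who follows the text would run the teacher comparison without covariates. Teachers in the three groups may differ in characteristics that relate to depression, anxiety, well-being or perceived safety whether or not a shooting occurred. An unadjusted test attributes those differences to exposure.

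This goes beyond a covariate list left to a fuller document. The article names a method for teachers that has no place for covariates, while another section promises control that it does not connect to this test.

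**Working it through.** **1. Does any other section attach covariates to the teacher test?**

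- Independent Covariates names conditional logistic regression, a model that does not appear in the Data Analysis Plan. The covariates it lists describe schools and districts, not teachers. Its closing sentence on propensity and control methods is general: it is not limited to students, but it is not linked to the teacher ANOVA either.
- The later multiple regression in the Data Analysis Plan covers school staff. It addresses the association between safety interventions and mental health, not the difference between exposure groups.

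So the stated teacher group comparison is unadjusted.

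**2. What does the matching cover?**

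Six exposed schools are matched to six nonexposed schools on state, urban status and school level. This gives teachers partial control for those three variables in the exposed-versus-never contrast. It does not balance teacher characteristics.

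The analysis also splits the exposed schools 3 and 3 (Exposure School Selection) and compares three groups. Take a hypothetical case: all three recent schools are high schools and all three less recent ones are middle schools. The six controls are then three and three. Exposed versus never is balanced (3 of 6 against 3 of 6), but recent versus never is 3 of 3 high schools against 3 of 6. The actual imbalance cannot be known before schools are selected.

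**3. The plan's own power figure**

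The article says a medium effect is detectable for teachers and gives no number. Inputs: α = .05, power 0.80, 30-60 exposed and 30-60 nonexposed teachers, so N = 60-120. For a one-way ANOVA with k = 3 groups, noncentrality is f² × N on (k − 1, N − k) degrees of freedom.

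- N = 60: detectable f = 0.411
- N = 120: detectable f = 0.287

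If medium means f = 0.25 (an assumption), neither N reaches it with three groups. That is a separate matter and does not decide this point. The figures serve here as the baseline for the cost of adjustment.

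**4. Cost of teacher-level covariates**

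With c covariates the error degrees of freedom become N − k − c. If the covariates explain a share R² of the outcome variance, detectable f is multiplied by √(1 − R²). The R² values are assumed. Teachers are treated as independent throughout.

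| | N = 60 | N = 120 |
|---|---|---|
| No covariates | 0.411 | 0.287 |
| 5 covariates, R² = 0 | 0.413 | 0.287 |
| 5 covariates, R² = 0.10 | 0.391 | 0.272 |
| 5 covariates, R² = 0.30 | 0.345 | 0.240 |

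**5. Cost of school-level covariates**

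Once the model accounts for school, a group effect is judged against variation between schools. Residual school degrees of freedom are 12 − 3 = 9, less one per school covariate.

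| School covariates | Residual df | Critical F (2, df), 5% |
|---|---|---|
| 0 | 9 | 4.26 |
| 2 | 7 | 4.74 |
| 3 | 6 | 5.14 |

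The small cost in step 4 therefore does not carry over to school-level covariates.

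**6. Illustrative size of residual confounding (all inputs assumed)**

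Bias in SD units = correlation with outcome × imbalance between groups.

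- Low: 0.2 × 0.2 = 0.04 SD. High: 0.5 × 0.5 = 0.25 SD.

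For a two-group contrast with equal groups the standard error is 2/√N SD: 0.26 at N = 60 and 0.18 at N = 120. Under the normal approximation, with z = bias × √N / 2, the nominal 5% false-positive rate becomes:

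- N = 60: 5.3% (bias 0.04) to 16% (bias 0.25)
- N = 120: 5.6% to 28%

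**The case against.** The strongest reply is that the teacher group difference is a supporting comparison. The first research question, on exposed versus unexposed schools, concerns students only. Teachers enter through the questions on safety interventions, which are answered by multiple regression, a model that can take covariates. Matching already controls three school variables for teachers as well, the closing sentence of Independent Covariates is general, and a condensed article often leaves covariate lists to a fuller document. The three-group split also affects the student analysis, so it is not specific to teachers. Much of this stands. It limits the importance of the point, but it does not supply covariates to the test as written.

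A reader might infer three stronger things that the documents do not support:

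- **That the teacher comparison has no control for confounding.** It has some, through the matching. What remains is teacher characteristics, unmatched school factors and possible imbalance within each exposed stratum.
- **That adjustment is free.** This is close to true for teacher-level covariates in a calculation that treats teachers as independent. It is not true for school-level covariates with 12 schools.
- **That teacher and student results lose comparability because only one is adjusted.** No teacher-versus-student contrast is planned, and among the mental health measures only the WHO-5 is common to both.

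The size is also fairly challenged. Neither the imbalance nor the correlation comes from the documents. Biases up to 0.15 SD would be below one standard error even at N = 120 (0.18 SD).

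**Conclusion.** The point holds as a cheap improvement. Followed as written, the plan gives an unadjusted teacher comparison across three non-randomised groups, although teacher demographics are collected and another section promises control. Partial control by matching means the contrast is open to residual confounding; it is not wholly uncontrolled.

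The bias of 0.04-0.25 SD, and the false-positive rates derived from it, are illustrations under assumed imbalance and correlation, not estimates for this study. Two things rest on the documents themselves: the mismatch between the stated student and teacher methods, and the gap between Independent Covariates and the Data Analysis Plan. The limit of 9 residual school degrees of freedom follows from 12 schools in three groups and applies to any model that treats school as the unit of exposure.

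**What to change.** - Replace the teacher ANOVA with a covariate-adjusted model that accounts for school, using a short prespecified list of teacher-level characteristics already collected. Report the unadjusted comparison alongside.
- Name the covariates from what the teacher survey actually records. Demographics gives only length of time at the school as an example for teachers; sex, race and age are listed there for students.
- Justify any use of length of time at the school. Staff turnover may follow a shooting, and the variable bears on whether a teacher was present, so adjusting for it could remove part of the exposure effect.
- Keep school-level covariates to a minimum. Two would leave 7 of the 9 residual school degrees of freedom.
- Reconcile Independent Covariates with the Data Analysis Plan: state whether the covariate and propensity methods apply to the teacher comparison, and in which model.

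The cost is a change of wording and a few degrees of freedom, with no new data. It is best fixed before teacher outcomes are analysed.
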